#### Agency

*Sense of control* is measured using an 8-item index on a Likert scale ranging from 1 “strongly disagree” to 4 “strongly agree.” This scale offers an unbiased estimate of personal control/powerlessness and demonstrates high reliability (alpha = 0.83) [56].

The *Self-Efficacy Scale* is a 9-item scale reflecting the confidence of the individual that they can cope with high-risk situations without relapsing [57]. Self-efficacy is among the strongest and most-studied predictors of smoking cessation treatment outcomes [58–60].

Coping is assessed using the eight-item *Daily Coping Inventory* [61, 62]. The measure includes eight coping dimensions including situation redefinition, direct action, catharsis, acceptance, seeking social support, distraction, religion, and relaxation. The original instructions were modified to assess coping related to problems and events that occurred in the past week (rather than day), and read as follows, “Please think about the events and problems that bothered you most over the last week and decide which choices best describe you. Then choose your answer.” Each item is rated on a 5-point Likert response scale ranging from “strongly disagree” to “strongly agree.” Each coping dimension is represented by a single item. Higher scores reflect greater reliance on a particular coping dimension. Catharsis and seeking social support are associated with relatively high levels of negative affect, and acceptance is associated with relatively low levels of negative affect and relatively high levels of positive affect. Use of distraction and relaxation is associated with relatively high levels of positive affect [61, 62].

#### Stress/negative affect and psychological distress

The *Perceived Stress Scale-4 (PSS-4)* [63] is a four-item measure designed to assess the degree to which respondents find their lives to be stressful. Internal consistency is good and PSS-4 scores are predictive of relapse [64–66].

The *Positive and Negative Affect Schedule (PANAS)* comprises two mood scales: Positive Affect (PA) and Negative Affect (NA). Internal consistency for both scales is good, and negative affect scores have been among the best predictors of relapse in previous studies [58, 67, 68]. Elevated scores on these scales are indicative of greater positive affect or negative affect, respectively [69].

The *Patient Health Questionnaire* (PHQ-8) is an eight-item sale which can be used to establish provisional diagnoses for selected DSM-IV disorders. All forms are well validated and shortened forms of the PHQ, like the PHQ-*, are often used when depression and/or anxiety are of interest in a research setting. We are using the PHQ-8 in lieu of the PHQ-9 because the nature of the trial will prevent us from following up with the necessary clinical review and immediate response required when someone responds as suicidal on the final question of the PHQ-9. The PHQ-8 is scored the same as the PHQ-9 and just as sensitively detects levels of depression and anxiety [70–72].

#### Patient reported outcomes

The *Functional Assessment of Cancer Therapy – Cervix Cancer (FACT-Cx)* comprises all items from the FACT-G and the Cx subscale. The FACT-G (version 4) is a 27-item self-report quality of life measure developed and validated among cancer patients and survivors. It consists of four subscales measuring physical well-being, functional well-being, social/family well-being, and emotional well-being. Each subscale produces a score that can be aggregated into one total score. The Cx subscale contains 15 items concerning symptoms and concerns specifically related to cervical cancer developed by cervical cancer patients and clinicians. The Fact-Cx can be self-administered or used in an interview format. Individuals are asked to report how they feel today and how they have felt during the previous 7 days, with higher scores indicating better quality of life. Cronbach’s alphas for each subscale are good and have been reported as follows: psychical well-being (0.82), functional well-being (0.80), social/family well-being (0.69), emotional well-being (0.74), and total FACT-G (0.89) [73, 74].

*The Fear of Cancer Recurrence Inventory – Short Form (FCRI-SF) is a* multidimensional self-report scale designed to assess a patient’s fear of cancer recurrence [75, 76]. This measure was modified to assess fear of developing cancer for participants with a history of CIN [15, 77].

#### Smoking abstinence

*Self-report smoking abstinence* assessments are based on recommendations from the Society for Research on Nicotine and Tobacco (SRNT) [30] and include abstinence assessments at all follow-up assessments. We are evaluating two point-prevalence abstinence measures: (1) no smoking during the previous 7 days, and (2) no smoking during the previous 30 days. Point-prevalence abstinence rates (intent-to-treat) will be estimated using generalized estimating equations.

*Biochemically verified abstinence.* Biochemically verified abstinence is assessed using saliva cotinine [29]. Participants who report 7-day point-prevalence abstinence at any follow-up assessment are mailed a prepaid envelope, instructions for providing a saliva sample, and a saliva collection kit. Research staff are available to speak with participants by phone and/or email should the participant have questions about the collection process. The participant is asked to return the sample via mail using a pre-paid envelope and, upon receipt of returned saliva samples, participants are compensated $30.

*Smartphone assessments*. All participants are asked to complete brief monthly assessments through REDCap (sent via SMS) for 24 months. For participants randomized to MAPS+, these 5-item monthly assessments are used to check in and offer personally tailored treatment content delivered via text messages and matched on both (1) areas in which participants indicate a need for support, and (2) smoking status, perceived stress, motivation, and self-efficacy. Participants randomized to ST also receive monthly assessments of smoking status, perceived stress, motivation, and self-efficacy (four items) to ensure that both treatment conditions are matched on assessment contacts. However, ST participants do not receive additional treatment after completing these monthly assessments.

*Primary and secondary outcomes*. Our primary outcome is self-reported 7-day point prevalence abstinence at 24 months where participants who report no smoking in the previous 7 days are considered abstinent. This follows recommendations for community-based smoking cessation trials that do not involve in-person assessments [29, 30]. Secondary outcomes are biochemically verified abstinence, length of abstinence, continuous abstinence, cigarettes per day, and quit attempts.

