**Fig. 1 Fig1:**
[figure not shown]
Study flow

ST participants are electronically connected with Tobacco Free Florida (i.e., the Florida Quitline). MAPS + consists of 6 proactive MAPS-based phone counseling sessions over 12 months plus a novel digital treatment adjuvant, which is delivered over 24 months. All participants receive 12 weeks of combination nicotine replacement therapy (patches + lozenges). Assessments are completed at baseline, 3, 6, 12, 18 and 24 months following baseline. All assessments are completed remotely (over the phone or via a secure REDCap link). In addition, brief REDCap-based smartphone assessments are delivered every 30 days, which are used to drive the personalized text-based treatment content in the MAPS + condition, are administered throughout the 24-month treatment period. These assessments are also delivered to ST participants to ensure that both treatment conditions are matched on assessment burden. The primary outcome is self-reported 7-day point prevalence abstinence over time throughout the 24-month assessment period [29, 30]. Secondary outcomes include additional smoking-related outcomes (i.e., biochemically verified abstinence, length of abstinence, continuous abstinence, cigarettes per day, quit attempts).

It is hypothesized that self-reported, 7-day point prevalence abstinence rates will be greater in MAPS + than in ST over time throughout the 24-month assessment period. For secondary outcomes, it is hypothesized that MAPS+ (vs. ST) participants will have higher biochemically confirmed abstinence rates at 24 months and across all assessments, make more quit attempts, report longer periods of abstinence, and report smoking fewer cigarettes per day across all assessments throughout the 24-month study period.

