### Procedures

This study was reviewed and approved by Advarra, the H. Lee Moffitt Cancer Center institutional review board (IRB) and is registered on ClinicalTrials.gov (NCT05645146). After completion of a brief online pre-screener, potential participants are contacted by research staff via phone to complete a more detailed screening. All eligible individuals are invited to participate. A detailed description of the study is provided, and verbal informed consent is obtained. Individuals who decline or are ineligible are referred to other cessation programs. Individuals who meet all eligibility criteria and consent to participating in the study complete the baseline assessment either over the phone with a research coordinator or via a secure electronic REDCap link sent via text message or email based on their preference. Following completion of the baseline assessment, participants are randomized to MAPS + or ST using a 1:1 ratio with a block size of 4 following stratification on the following variables: daily vs. nondaily smoking; CIN and early cancer stages (Stages I and Stage II) vs. advanced cancer stages (Stage III and Stage IV), and pending or in active treatment vs. completed treatment. The randomization sequences were created by the study statistician and implemented in REDCap.

Assessments occur at baseline, 3, 6, 12, 18 and 24 months and take approximately 20 min to complete (see Table 1). Participants are given the option to complete the assessments via phone or via a hyperlink as a REDCap-administered self-assessment. Compensation is provided after each assessment is completed (6 assessments x $30 = $180). Participants who report abstinence at any follow-up point are mailed a cotinine test. Compensation for returning cotinine tests is $30 per assessment.

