### Nicotine replacement therapy

All study participants receive 12 weeks of combination nicotine replacement therapy (patches + lozenges). Nicotine patches provide a low, constant level of nicotine, which attenuates nicotine withdrawal symptoms, and lozenges help with managing acute cravings to smoke. When combined with behavioral treatment, NRT doubles the odds of successfully quitting [26]. All participants receive educational materials describing potential side effects, proper use of the patch, and an illustration demonstrating the proper placement of the patch on the body. The nicotine patch and lozenge regimens are based on each participant’s self-reported smoking rate. Participants who smoke > 10 cigarettes/day receive 8 weeks of 21 mg patches, 2 weeks of 14 mg patches, 2 weeks of 7 mg patches, and 12 weeks of 2 mg lozenges. Those who smoke < = 10 cigarettes/day receive 8 weeks of 14 mg patches, 4 weeks of 7 mg patches, and 12 weeks of 2 mg lozenges.

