#### Demographics, smoking history, alcohol and substance use, and health history

Demographic variables assessed include age, race, ethnicity, education, income, gender identity, sex assigned at birth, marital status, sexual orientation, occupational status and insurance status. Smoking history is assessed by asking about years smoking, preferred brand of cigarettes, quitting history, partner smoking, and the presence of other people who smoke in the household. The use of e-cigarettes (vaping) is also assessed. History of alcohol use is assessed using NIAAA core items [35, 36]. Substance use history is assessed with three items asking about illegal substance use in the past year.

History of CIN or cervical cancer is assessed by asking about diagnostic history, dysplasia grade or cervical cancer stage at the time of diagnosis, current CIN or cervical cancer stage, time since diagnosis, treatment status and time since completion of treatment.

The *Cancer Patient Tobacco Use Questionnaire (C-TUQ)* is a 22-item self-report survey designed to capture information about tobacco use by cancer patients and cancer survivors. The items are specifically tailored to the trajectory of cancer diagnosis, treatment, and survivorship. The C-TUQ survey tool is divided into five domains and includes a Core (short form of 4 items) and an Extension. The questionnaire is intended to be administered at key time points during periods of cancer treatment and recovery [37].

Nicotine dependence is assessed using the *Heaviness of Smoking Index (HSI)*. The HSI comprises two items from the Fagerstrom Test for Nicotine Dependence (FTND): self-reported average number of cigarettes smoked per day (CPD) and time to first cigarette upon waking (TTFC). The HSI is a good indicator of nicotine dependence, has fair internal consistency and is predictive of smoking relapse [38].

*The Wisconsin Index of Smoking Dependence Motives – Short Form (WISDM-37)* comprises 37 items designed to assess 11 different motivational domains: affective enhancement, affiliative attachment, automaticity, loss of control, cognitive enhancement, craving, cue exposure/associative processes, social/environmental goads, taste/sensory properties, tolerance, and weight control [39, 40].

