## Discussion

Given that cervical cancer survivors are more likely than other subgroups of cancer survivors to smoke, and that individuals with a history of CIN who smoke are at substantially elevated risk for developing cervical cancer, there is a pressing need to target these subpopulations with efficacious smoking cessation treatment. MAPS + builds on prior evidence that MAPS-based tobacco treatment is efficacious for individuals with a history of CIN or cervical cancer and meets the need for extended support for these vulnerable populations.

This study is the first to specifically target and address the smoking cessation treatment needs of individuals with a history of CIN or cervical cancer over an extended, two-year period. MAPS + is highly flexible and designed to specifically target individuals who have varying levels of motivation to quit with treatment content specifically designed to meet their unique treatment needs over an extended treatment period. If found efficacious, MAPS + is likely to represent a sustainable, low-burden and engaging approach with broad reach and dissemination potential. For example, MAPS + could be disseminated within a variety of outreach programs and community-based networks targeting individuals with a history of CIN or cervical cancer. An important strength of our study is that individuals who are not yet ready to set a quit date are eligible to enroll. Two-thirds (i.e., 67%) of participants in our prior trial reported that they were not ready to quit at the time of study enrollment, [15] highlighting the importance of engaging these individuals in tobacco cessation treatment in an acceptable way. The Wellness Program component within MAPS + allows individuals who are not yet ready to commit to quitting smoking to focus on other life issues that are particularly salient for them (e.g., stress, family issues, finances, adjustment to a cancer diagnosis, fear of developing cancer or cancer recurrence).

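### Cotinine is the only named verification marker from month 3 although everyone is given 12 weeks of nicotine replacement, so some true quitters may fail verification in the secondary verified outcome

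*Protocol article*

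**What the plan says.** All points are from the protocol article.

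- **Marker** (Smoking abstinence): "Biochemically verified abstinence is assessed using saliva cotinine". No second marker is named.
- **Trigger** (Smoking abstinence): "Participants who report 7-day point-prevalence abstinence at any follow-up assessment are mailed a prepaid envelope", with a saliva kit.
- **Schedule** (Procedures): "Assessments occur at baseline, 3, 6, 12, 18 and 24 months". Month 3 is therefore the first visit with verification.
- **Supply** (Nicotine replacement therapy): "All study participants receive 12 weeks of combination nicotine replacement therapy (patches + lozenges". This applies to both arms.
- **Use of the outcome** (Study design overview): the secondary hypothesis is that MAPS+ will show "higher biochemically confirmed abstinence rates at 24 months and across all assessments". The analytic plan for the primary outcome adds that comparable models will be used for secondary outcomes, so month 3 enters the verified comparison.
- **Other nicotine**: on smoking history, the article says "The use of e-cigarettes (vaping) is also assessed". Table 1 schedules smoking history at baseline only and lists no dedicated measure of current nicotine replacement use at any visit. The C-TUQ is repeated at every follow-up, but its items are not listed.
- **Primary outcome** (Smoking abstinence): "Our primary outcome is self-reported 7-day point prevalence abstinence at 24 months". It does not depend on cotinine.

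**The concern.** Cotinine is a metabolite of nicotine whatever the source. The trial supplies nicotine to everyone for about the length of time that leads up to the first verified visit, then uses a nicotine metabolite to confirm that people are not smoking. A self-reported quitter who is still using patches or lozenges, or who vapes, cannot be confirmed abstinent by this test.

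The behavioural arms can hardly be masked and the primary outcome is self-reported, so the verified outcome is the only objective check the article describes. If part of it reflects product use, agreement or disagreement between the self-reported and verified results is harder to interpret. A dip in verified abstinence at month 3 that clears later would also feed into the time and group-by-time terms of the longitudinal model.

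**Working it through.** **1. The plan's own figure.** Power and sample size gives 16% (ST) and 29% (MAPS+) at 24 months, 170 per group, two-sided alpha 0.05 and power of at least 0.80. With a two-proportion z-test:

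- pooled standard error = √(2 × 0.225 × 0.775 / 170) = 0.0453
- unpooled standard error = √((0.16 × 0.84 + 0.29 × 0.71) / 170) = 0.0447
- power = Φ((0.13 − 1.96 × 0.0453) / 0.0447) = 0.82

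A Wald test on the log odds ratio gives 0.81. The stated figure reproduces. It concerns self-report, so nothing below changes it. The article gives no power for the verified outcome.

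**2. Timing.** The supply lasts 12 × 7 = 84 days. Month 3 is 365.25 / 4 ≈ day 91, and the kit is mailed after abstinence is reported. A full course begun at baseline ends about 7 days before the visit, and I treat such a participant as clear. Overlap needs a later start, slower use, extra product or vaping. A late start is plausible because the trial enrols people not ready to quit. The Discussion says: "Two-thirds (i.e., 67%) of participants in our prior trial reported that they were not ready to quit at the time of study enrollment". Late or slow use could also carry some exposure past month 3.

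**3. Size at month 3 (illustration).** Let f be the share of true quitters who use nicotine products at sampling and are not verified. Then verified rate = true rate × (1 − f). The documents give neither f nor a month-3 abstinence rate. I borrow 16% and 29% and vary f.

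| f in ST | f in MAPS+ | ST verified | MAPS+ verified | Difference (points) | Odds ratio | Power at 170 per group |
|---|---|---|---|---|---|---|
| 0 | 0 | 16.0% | 29.0% | 13.0 | 2.14 | 0.82 |
| 0.10 | 0.10 | 14.4% | 26.1% | 11.7 | 2.10 | 0.77 |
| 0.25 | 0.25 | 12.0% | 21.75% | 9.75 | 2.04 | 0.67 |
| 0.50 | 0.50 | 8.0% | 14.5% | 6.5 | 1.95 | 0.48 |
| 0.25 | 0.50 | 12.0% | 14.5% | 2.5 | 1.24 | 0.10 |
| 0.50 | 0.25 | 8.0% | 21.75% | 13.75 | 3.20 | 0.95 |

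Equal shares shrink the difference by the factor 1 − f but move the odds ratio little. Unequal shares can push it either way. The difference is unchanged when 29 × f(MAPS+) = 16 × f(ST), that is when the MAPS+ share is 16/29 = 0.55 of the ST share. Below that ratio the difference widens.

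**4. Size across visits.** Suppose only month 3 is affected and the true difference is 13.0 points at all five follow-ups. The simple average is (4 × 13.0 + month-3 difference) / 5:

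- f = 0.25 in both arms: (52 + 9.75) / 5 = 12.35 points
- f = 0.50 in both arms: (52 + 6.5) / 5 = 11.7 points
- 0.25 in ST and 0.50 in MAPS+: (52 + 2.5) / 5 = 10.9 points
- the reverse: (52 + 13.75) / 5 = 13.15 points

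**The case against.** The strongest reply is that the article does not say how a positive sample from a nicotine replacement user is classified. It gives no cut-off and no rule, and both are commonly left to a full protocol or analysis plan. That stands. A reader might infer that quitters on nicotine replacement are counted as smoking; the article nowhere says so. What survives is that a positive cotinine cannot confirm abstinence in such a person, and that a later rule needs data on product use at sampling. The article does not show that these data are collected. The C-TUQ may cover part of this; its items are not listed, so neither coverage nor a gap can be asserted.

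A second reply is that the supply nominally ends before month 3. That also stands, and it rules out the reading that verification at month 3 measures nicotine use instead of smoking. Only late, slow or additional users and vapers are at risk.

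A third is that nothing shows which arm uses more. Both receive the same supply, so the inference that MAPS+ would be penalised has no support in the documents. The last row of the table shows the opposite case.

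Finally, classing every cotinine-positive product user as abstinent would return those cases to self-report and weaken the check. That is a fair objection to making such a rule the only one.

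**Conclusion.** The point holds within limits. Using cotinine alone from month 3, in a trial that supplies nicotine for 12 weeks, exposes the verified secondary outcome to misclassification. The main exposure is at month 3 and in the comparison across all assessments. The 24-month verified comparison is largely spared, apart from anyone vaping or using nicotine products then. The self-reported primary outcome and its power are untouched.

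The effect could be appreciable at month 3 and is modest when averaged over five visits, unless use differs sharply by arm. These sizes rest on assumed use shares, on month-24 rates borrowed for month 3, and on the assumption that users with positive samples are not verified. The direction cannot be stated from the documents.

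**What to change.** 1. Ask about past-week nicotine replacement and e-cigarette use with every saliva kit.
2. Define the across-assessment verified analysis on months 6, 12, 18 and 24, and show month 3 separately.
3. For cotinine-positive self-reported abstainers who report non-cigarette nicotine, report verified abstinence both ways: strict (not verified) and lenient (not classed as smoking). State in advance which is the main version.

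The cost is one or two extra items per kit, one visit fewer of five in the verified comparison, and reliance on self-report in the lenient version. Treatment and sample size do not change. The article describes recruitment as ongoing, so the items can still be added, but product use cannot be recovered for samples already taken without them.

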### General analytic approach

We hypothesize that self-reported 7-day point prevalence abstinence rates will be greater in MAPS + than in ST. All data analyses will be performed using SAS version 9.4 with significance set at 0.05 for statistical tests of primary hypotheses. Descriptive statistics will be used for initial review of distributions and determination of needs for transformation prior to primary analyses. Group differences in baseline measures will be assessed and any variable that exhibits a group difference at p < .10 will be added as a covariate in the primary analyses.

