### Statistical analysis

#### Analytic plan for primary outcome

Logistic regression will assess treatment group differences in self-reported 7-day point prevalence abstinence at 24 months. Generalized estimating equations (GEE) will fit population-averaged models of longitudinally measured self-reported 7-day point prevalence abstinence, with the main covariates of treatment group, time (months from baseline), and the interaction of group and time. The GEE analysis permits evaluation of aggregated intervention effects across assessments, changes in abstinence over time, and group differences in changes (interaction term). These models will include any covariates found to differ by group (p < .10) despite randomization. Comparable models will be applied to evaluate treatment differences for secondary outcomes.

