### Power and sample size

The primary statistical analyses will evaluate intervention effects on 7-day point prevalence abstinence. This will be done in two ways: (1) using logistic regression at 24 months, and (2) using GEE to assess intervention effects aggregating across all assessments. Based on results from our recently completed trial [15], abstinence rates in both groups are expected to increase over time along with an increasing difference between groups. Estimated abstinence at 24 months is 16% for ST and 29% in MAPS+. PASS 2020 [85] was used to estimate sample size/power for logistic regression analyses. With a sample size of 170 per group, power is ≥ 0.80 for logistic regression analyses at 24 months with alpha = 0.05 and a two-sided test. Using GEESIZE 3.1, [86] power ≥ 0.95 for GEE analysis of abstinence across all follow-ups. No adjustments to enrollment size will be needed to account for attrition as we will utilize multiple imputation to manage missing data.

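### The article names two primary outcomes, abstinence at 24 months and abstinence over time, tests both as primary at 0.05, and does not say which result decides the trial

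*Protocol article*

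**What the plan says.** The primary outcome is defined twice in the protocol article.

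- Study design overview: "The primary outcome is self-reported 7-day point prevalence abstinence over time throughout the 24-month assessment period". The hypothesis there has the same scope: abstinence is to be higher in MAPS+ "than in ST over time throughout the 24-month assessment period".
- Smoking abstinence, in the paragraph on primary and secondary outcomes: "Our primary outcome is self-reported 7-day point prevalence abstinence at 24 months".

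General analytic approach restates the hypothesis without a time point: "We hypothesize that self-reported 7-day point prevalence abstinence rates will be greater in MAPS + than in ST". It fixes the level, "with significance set at 0.05 for statistical tests of primary hypotheses".

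Analytic plan for primary outcome lists a logistic regression at 24 months and a GEE over the repeated assessments, "with the main covariates of treatment group, time (months from baseline), and the interaction of group and time". It says the GEE allows aggregated effects, change over time and group differences in change to be evaluated.

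Power and sample size treats both as the primary analyses: "This will be done in two ways: (1) using logistic regression at 24 months, and (2) using GEE to assess intervention effects". It gives power for each: at least 0.80 for the 24-month test and at least 0.95 for the GEE.

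**The concern.** Abstinence at 24 months and abstinence averaged over five visits are different quantities. They answer different questions about a treatment meant to sustain abstinence. The article does not say which one decides, whether both must succeed, or what is concluded if one is significant and the other is not.

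Two things are at stake. If a positive result on either test is taken as success, the error rate for the primary claim is above its nominal level. And if the results split, the choice of headline would be made after seeing the data. The article itself gives reason to expect a possible split: it reports that the earlier MAPS effect was significant at 12 months and no longer so at 18 months.

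**Working it through.** **Inputs from the article.** 16% (ST) and 29% (MAPS+) abstinent at 24 months, 170 per group, two-sided 0.05 (Power and sample size); follow-up at 3, 6, 12, 18 and 24 months (Study design overview).

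**Assumptions.** The within-person correlation ρ is not given. I take it as exchangeable, 0.2 to 0.8, with complete data and the aggregated effect as the equal-weight average of the five visits.

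**1. The plan's own figure.** Mean rate 0.225.
- SE under no difference = √(2 × 0.225 × 0.775 / 170) = 0.0453.
- SE under the alternative = √((0.16 × 0.84 + 0.29 × 0.71) / 170) = 0.0447.
- Power = Φ((0.13 − 1.96 × 0.0453) / 0.0447) = Φ(0.92) = 0.82.

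The stated power of at least 0.80 is reproduced (a Wald test on the log odds ratio gives 0.81). The GEE figure cannot be checked, because its visit rates and correlation are not given.

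**2. Correlation of the two tests.** With equal variance per visit, the five-visit mean has variance (1 + 4ρ)/5, and its covariance with the 24-month value is the same. So r = √((1 + 4ρ)/5).

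**3. Familywise error** = 1 − P(|Z₁| < 1.96 and |Z₂| < 1.96), bivariate normal with correlation r. False claims favouring MAPS+ are about half of it.

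| ρ | r | Either test, two-sided | Favouring MAPS+ (nominal 0.025) |
|---|---|---|---|
| 0.2 | 0.600 | 0.0875 | 0.044 |
| 0.3 | 0.663 | 0.0851 | 0.043 |
| 0.5 | 0.775 | 0.0796 | 0.040 |
| 0.7 | 0.872 | 0.0729 | 0.036 |
| 0.8 | 0.917 | 0.0687 | 0.034 |

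Independent tests would give 1 − 0.95² = 0.0975. An AR(1) correlation of 0.5 to 0.9 gives 0.088 to 0.072.

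**4. Can the tests disagree?** Illustration with assumed differences of 8, 10, 14, 10 and 6 points. The average is 48/5 = 9.6 points, which is 1.6 times the 24-month difference. For ρ from 0.3 to 0.7 the standard error of the average is 0.663 to 0.872 times that of one visit. The signal-to-noise ratio is therefore 1.6/0.872 = 1.8 to 1.6/0.663 = 2.4 times as large. At 24 months, 16% against 22% gives power 0.29. So the average can well be significant where the 24-month test is not. Under the article's own assumption of a growing difference, the split runs the other way and the 24-month test is the stronger one.

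**5. Cost of the options.**
- One deciding test at 24 months, alone or first in a fixed order: power 0.82, N unchanged.
- Both kept, with 0.025 each: Φ((0.13 − 2.241 × 0.0453) / 0.0447) = Φ(0.64) = 0.738. Restoring 80% takes 195 per arm, 390 in total.

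**6. The GEE contrast.** With time as continuous months, logit p = β₀ + β₁·group + β₂·t + β₃·group·t, so the group log odds ratio at month t is β₁ + β₃t. At t = 0 this is β₁. The mean visit time is (3 + 6 + 12 + 18 + 24)/5 = 12.6, so the average over the five visits is β₁ + 12.6β₃.

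**The case against.** The strongest reply is that an article condenses a fuller plan, which may name the deciding test. That would cover a missing detail. It does not cover two different definitions in the text, carried into the analysis and power sections.

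Several stronger readings are tempting, and the article does not support them.

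- **That the error rate for concluding MAPS+ works exceeds 5%.** The 0.07 to 0.09 counts false findings in either direction. Those favouring MAPS+ are about 0.034 to 0.044. That is inflated against 0.025, but below 0.05.
- **That the error is near 0.12.** This counts the group-by-time interaction as a third route to success. The article lists the interaction as a description of differing change. Its hypothesis concerns abstinence rates.
- **That the earlier trial's effect was gone at 24 months.** The article reports loss of significance at 18 months. It gives no 24-month result, and a non-significant effect is not an absent one.
- **That the GEE cannot deliver an aggregated effect, or would test month 0 with far less power than claimed.** The aggregated effect is an ordinary contrast of the listed terms. The article never equates it with the group coefficient and does not say whether time is continuous or categorical. Any power for that coefficient depends on visit rates that the article does not give, so the 0.95 is not shown to be wrong.

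**Conclusion.** The contradiction stands and needs to be resolved: the article does not establish which result decides the trial. This part rests on the text alone.

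The inflation is moderate. It applies if success on either test is accepted, and its size depends on the assumed correlation, the equal-weight average and complete data. The illustration of disagreement shows only that a split is realistic. It is not a forecast of how often one will occur.

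The GEE point is secondary: the contrast should be named, but the model is not defective.

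**What to change.** Name one primary outcome and one deciding test, and make Study design overview, Smoking abstinence, General analytic approach, Analytic plan for primary outcome, and Power and sample size agree. One workable choice is 7-day point prevalence abstinence at 24 months at two-sided 0.05. It is the outcome for which the article gives its event rates, and it fits the aim of long-term abstinence. The longitudinal GEE then becomes a key secondary, tested at 0.05 only if the 24-month test is significant.

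In the same edit, state which GEE contrast is the aggregated effect, for example the average of the visit-specific group effects. If time enters as continuous months with the interaction, the group coefficient alone is the effect at month 0 and should not be reported as the aggregate.

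The cost is a change of wording, in any SAP or registry entry that differs as well, and the loss of one route to a positive claim. Sample size and 24-month power do not change. The article describes recruitment as ongoing. The change should be dated and made before unblinded outcome data are seen.
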